**[name]**

Conduct blinded ankle ROM assessments and deliver questionnaires to participants at entry into study, after 6 weeks of treatment, after 12 weeks of treatment and 1 year after entry into study.

Direct participants in completing questionnaires ie participant to enter study ID # and time point in study (entry into study, after 6 weeks of treatment, after 12 weeks of treatment and at 1 year after entry into study)and deliver to front desk for storage in locked cabinet.

Remain blinded to participant allocation. Report patient unblinding.

**[name]**

Conduct initial phone screen (with [name] and [name]).

Interpret UTC images (with [name]).

Maintain study ethics.

Review unanticipated problems, report to CREB if necessary as soon as reasonably possible.

Data audits.

Financial reporting to UBC.

Liase with UBC statistical services.

Retain hard copies of patient data in secure area for 7 years following study publication.

**UBC statistical services**

Analyze the data at midpoint of recruitment

Statistical analysis after target number (n=42) have passed 3 month time point.

**Study Flow Chart**

**Physical Examination**

Physical examination will incorporate a standard physiotherapy assessment, a standard IMS assessment, and a specific assessment of the Achilles tendon itself by an experienced practitioner (LS). The physiotherapy assessment will include examination of the lumbar spine, pelvis, hip, knee, ankle and foot as relevant. Examination of these regions, as appropriate, will include: range of motion assessment; muscle length tests; manual muscle testing; observation of alignment/symmetry; and foot architecture (subtalar or forefoot varus; cavus or pronated foot). Biomechanical issues that could be expected to have an impact on the magnitude of strain delivered to the Achilles tendon will be addressed on an individual basis.^57 58^

The IMS assessment is targeted to observe for the presence of neuropathic change, as operationally defined by Gunn, and will be derived from the general and region-specific examination protocol he describes.^49^ Manifestations of neuropathic change that may be observed clinically include: sensory manifestations (hyperpathia and allodynia), autonomic manifestations (vasoconstriction, sudomotor activity, pilomotor reflex, trophedema and trophic changes in skin, hair and nails) and motor manifestations (muscle shortening, limitation of joint range and enthesopathy). When neuropathic change is present, there is typically a mixture of sensorimotor and autonomic disturbances evident, with findings grouped in a segmental distribution that indicate the affected spinal level(s) and muscles involved. Aspects of the Gunn IMS examination that may not already have been assessed in the standard physiotherapy assessment include: observation of posture and gait, any obvious muscle wasting or dermatomal hair loss; quick screening tests; neurological examination of the L2 to S1 segments in terms of power and reflexes; straight leg raise test of neural provocation; and specific motor, sensory and autonomic neuropathic assessments. Observation of posture allows for the detection of variations in spinal curvature (scoliosis or anomaly of the normal kyphotic and lordotic curvatures) and asymmetries in the shoulder or pelvic girdles. Quick tests include Trendelenburg’s sign (to assess for weakness in the gluteal muscles, especially gluteus medius), squat (to screen the hip and knee joints), and FABERE/Patrick’s test for limitation of hip joint range. The regional part of the IMS examination for pain in the calf, in this investigation, will be looking specifically for patterns of neuropathic change in the L5-S2 segments. These levels are of key significance as they comprise the nerve supply to the gastrocnemius and soleus muscles i.e. S1 and S2 from the tibial nerve (L4-S3)^59^, and to the Achilles tendon itself i.e. the sural nerve (derived mostly from the S1 segment but also from L5 and S2).^60^ Although spinally the focus will be on the lumbar region, assessment (and treatment) will extend into the thoracic spine as recommended by [name].^49^ The spine will be palpated for prominent and tender spinous processes which may be an indicator of dysfunction at that level. Hyperpathia will be tested paraspinally by running a pin down the body, crossing dermatomes. Skin temperature will be palpated to assess for any obvious coolness (vasoconstriction). The Skin Rolling and Matchstick tests for trophedema will be conducted. Observation will be made for the presence of: a peau d’orange effect (trophedema); excessive sweating (sudomotor activity); “goosebumps” (pilomotor reflex); and trophic changes in skin, hair (dermatomal loss) and nails. The lumbar back muscles, innervated by the dorsal rami of the spinal nerves, including the long polysegmental muscles (the thoracic components of the longissimus and iliocostalis lumborum) and the polysegmental muscles that attach to the lumbar vertebrae (the multifidus and the lumbar components of the longissimus and iliocostalis)^61^ will be assessed for the presence of painful tight bands. The deep muscles may only be fully assessed for signs of hypersensitivity by penetration with a needle. The peripheral muscles, innervated by the ventral rami of the spinal nerves, will also be assessed for the presence of painful tight bands.

Subjects with Achilles tendinopathy who do not demonstrate region-specific signs as defined by this assessment will be excluded from the study to reduce potential variability in treatment response.

The Achilles tendon will be assessed for the presence of tenderness on palpation of the mid-portion, with or without thickening of this region, and pain on tendon loading.^25 62^ Tendon loading will be achieved by asking subjects to perform heel raises (double or single), hopping or hopping forward as required to assess for a pain response.^62^

**IMS treatment group**

Intramuscular Stimulation (IMS) involves the insertion of fine sterile needles into tender and painful points in tight muscle bands (hypothesized in the IMS literature to be caused by reduced nerve supply).^49^ Needles inserted into muscles create an electrical discharge.^49^ In patients with chronic musculoskeletal pain syndromes, this discharge is strongly exaggerated and results in twitches, fasciculations or sustained contractions in the targeted muscle.^49^ Patients will feel these various muscular reactions, with the sustained contractions producing a distinctive deep aching sensation that is cramp-like in quality.^49^ This sensation is analogous to the Teh Ch’i or Deqi Phenomenon in Traditional Chinese Medicine Acupuncture (TCMA) literature.^49^ Treatment will be guided by the findings of the assessment, which will have paid particular attention to signs in groupings of muscles supplied by both the dorsal and ventral rami of the same segmental spinal level. Muscles in the periphery that have demonstrated tight bands or reduced muscle lengths will be treated with IMS by one of the investigators (LS). Muscles at levels of the spine that have demonstrated tight muscle bands, signs of trophedema or tender, prominent spinous processes will also be treated. Those muscles that respond to needle penetration with sustained contractions or “needle grasp”, such that resistance is felt on attempting to withdraw the needle, will be left in situ until the muscle releases. This may occur quickly, but may be expected to take up to twenty minutes.^49^ Those muscles that respond with only fasciculations or twitches may be treated with extra stimulation by “fanning” or “twirling”, depending on patient tolerance, but needles will then be promptly removed. Needles will also be briefly inserted into the Achilles tendon to produce a local inflammation-healing response.^49^ The IMS group will receive treatment once a week for the first six weeks of the trial and once every two weeks for the remainder, resulting in nine treatments overall.

**Sham needling**

The appropriate control for acupuncture or needling studies is always controversial, as the act of needling nonspecifically, even superficially, can induce a variety of physiological responses as well as a variable level of placebo response.^63^ Nonetheless, recently the importance of including both sham needling and no-treatment controls has been emphasized (c.f. section 6, and figure 1, in ^63^), and considered superior to non-penetrating “placebo needles.^63^ In the sham needling group, eight acupuncture needles will be inserted into the dermis (1-2 mm) of the buttock, posterior thigh and calf and will be left *in situ* for ten minutes. Points will be chosen that do not mimic either IMS or TCMA techniques. To avoid mimicking IMS treatment the needles will be inserted away from any tight muscle bands that may be present and will be inserted superficially so that no muscle penetration occurs. To avoid mimicking TCMA treatment, meridians in the treatment area and points used to treat heel pain specifically will be avoided, the depth of needle insertion will be superficial, and no “deqi” sensation will be elicited. Meridians in the area of the buttock (the bladder and Du meridians) are in the midline of the buttock and medial to this and so will not correspond with needle points used in IMS (more lateral). In the posterior leg, the bladder meridian is in the midline to the level of the inferior border of the gastrocnemius muscle and so will not correspond with IMS-targeted muscle banding (medial and lateral of the midline). Below the gastrocnemius muscle the bladder meridian moves laterally and so will not correspond with IMS needling of the Achilles tendon itself. No sham needles will be used in the area of the lower back or sacrum as the IMS points and TCMA points correspond more closely in this region. Particular care will be taken to avoid needling in the area of TCMA points used to treat heel pain specifically in the treatment area, these being: Bladder 57 (inferior edge of gastrocnemius muscle in midline) and Bladder 60 (in the depression midway between the lateral malleolus and the Achilles tendon, level with the high point of the bone), Kidney 4 (medial ankle, in the depression anterior to the angle formed by the Achilles tendon and the calcaneum), Gall Bladder 34 - “the physio point” (in the depression anterior and inferior to the head of the fibula) and Bladder 40 (at the mid-point of the transverse crease of the popliteal fossa).^64^

**Training program**

All three groups will undertake an exercise programme designed to initially maintain and then, as tolerated, increase the ability of the muscle-tendon unit and kinetic chain to absorb load. There will be four stages in this programme andEccentric exercises consisting of gastrocnemius-soleus-Achilles tendon complex loading (ELE) will be incorporated at each stage Eccentric loading has been demonstrated to be the most consistently effective conservative intervention in the treatment of mid-portion Achilles tendinosis.^25^ The program will be modeled on those developed by Alfredson and colleagues^27 65^ and Silbernagel and colleagues^48 66^. Eccentric exercises will be prescribed in a progressive manner for the twelve week duration of the trial. Exercise progression will be as follows: two-legged very slow (Stage 1a) to slow (Stage 1b) eccentric exercise to plantargrade (on flat ground) adding load with weighted backpack or resistance equipment as available (Stage 1a progressing to Stage 1b). The next level of exercises (Stage 2) will progress to single-legged slow eccentric exercise into dorsiflexion adding load with weighted backpack or resistance equipment as available Further progression of loading will then be achieved by introducing speed to previously prescribed exercises using only body weight as resistance (Stage 3). Those participants who reach Stage 4 will be prescribed sports specific exercises aimed at increasing the capacity of the muscle-tendon unit to absorb elastic loading to functional levels. Stage 1 exercises will be prescribed two to three times a day. Stage 1b exercises will be prescribed once a day, every other day. Stage 2 exercises will be prescribed every other day. Stage 3 exercises will be prescribed once a day every third day. All subjects on progression form Stage 1 to Stage 2 of the rehabilitation programme will have a scheduled rest day. On commencement of Level 2 exercises, Stage 1 and 2 level exercises will be alternated for 6 days of the week and the seventh day will be allocated a s a rest day. Once Stage 3 exercises are added, Stage 1, 2 and 3 exercises will be alternated for 6 days of the week and the seventh day will be allocated a s a rest day.

All subjects will be entered into the rehabilitation programme at Stage 1. Subjects will be progressed based on a twenty four hour response to exercise, specifically there must not be pain or stiffness the morning after undertaking the exercise. Pain during exercises will be allowed as long as it is not more than 5/10 pain on a zero to ten scale, where zero is no pain at all and ten is the worst possible imaginable pain. Through all four stages, those subjects in the IMS group and the sham needling group will be advised to rest from their ELE and exercise generally (including stretches) after their treatment for the remainder of the day and the entire next day. From Stage 2 on, this rest day will be scheduled to coincide with the day seven rest day that all groups will observe. They will be instructed to recommence their exercise program the morning after. This is standard advice given to patients receiving IMS treatment.

All subjects will be advised that they may participate in pain-provoking activity, such as running, as long as their pain does not reach greater than 2-3/10 (Visual Analogue Scale) during the activity and as long as pain has returned to baseline by the following morning. The provocation of this level of pain up to 5/10 VAS during rehabilitation has been shown to not hinder recovery.^48 66^

The exercise technique and progression will be reviewed every two weeks until 12 weeks (6 reviews total).

**Outcome measures**

The primary outcome measure for which the study is powered is the 12 week VISA-A score - a well validated and reliable disease-specific outcome measure, which also includes an activity-related pain scale.^67^ Secondary outcome measures include treatment success/failure, and muscle length (dorsiflexion ROM). Patients will rate themselves from 0 (very much worse) to 6 (very much improved). Scores of very much improved or much improved will be categorized as successes.^68^ Dorsiflexion range of motion with knee bent and straight will also be measured using an inclinometer, giving an indication of the effect of IMS and exercise vs exercise alone on muscle extensibility. These measures will be taken at 0 and 12 weeks, as well as at 52 weeks.[[1](#_ENREF_1)] After 12 weeks and 6 months of intervention, UTC scanning will be conducted to determine, as a pilot study, whether there is any subjective indication of a potential effect of IMS on tissue remodeling that could be pursued with a mechanistic study in future.

Muscle length measures will be made according to the protocol described by Norkin and White^69^ and Kendall and colleagues^70^ by a physiotherapist (MB) unaware of the treatment allocation. The two-joint plantarflexors (gastrocnemius and plantaris) will be measured in supine with the knee extended. The one-joint plantarflexors will also be measured in supine but with the hip and knee flexed 90 degrees or more to make the two-joint plantar flexors slack across the knee joint. The ankle will be passively dorsiflexed and the angle achieved measured by goniometry. The fulcrum will be centred over the lateral aspect of the lateral malleolus, the proximal arm will be aligned with the lateral midline of the fibula, using the head of the fibula for reference, and the distal arm will be positioned parallel to the lateral aspect of the fifth metatarsal. The ankle will be dorsiflexed to end-of-range (firm muscular end-feel) by pushing upward across the plantar surface of the metatarsal heads, without allowing the foot to rotate into inversion or eversion. Intratester reliability in measuring passive ankle dorsiflexion by goniometry has been shown to have an Intraclass Correlation Coefficient (ICC) of 0.91 for more experienced therapists.^71^ MB has had over three decades of musculoskeletal clinical experience.

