# Study Design

This is a prospective, single blind, randomized controlled trial with three groups. All groups will receive standard 12 week physiotherapy program provided by LS, including a standardized and progressive eccentric training and strengthening program. The first group will receive IMS (detailed below), while the second will receive an equivalent number of sham (superficial non-intramuscular) needling sessions. The third receives the progressive exercise training program alone. Patients will be recruited from the clinical practice of LS and colleagues; additionally, the study will be advertised through LS’s and AS’s contacts in the IMS, UBC, Physiotherapy Association of BC, and Vancouver Coastal Health networks. After providing informed consent and being screened for inclusion/exclusion criteria, diagnosis will be confirmed by physical examination. Inclusion criteria include subjects 19 to 60 years of age, fluent in English, with a 3 month minimum symptom duration, evidence of midportion Achilles tendinopathy on physical examination and tendinosis on ultrasound; and objective signs by Gunn IMS assessment of neuropathic change in the L5-S2 segmental levels including the presence of taut muscle bands amenable to IMS.^49^ Tight bands palpated in muscles paraspinally (dorsal rami) from T1 down and peripherally (ventral rami) from T12 down will also be treated in the IMS group, but participants without findings in the L5-S2 levels will be excluded to limit variability among subjects. Exclusion criteria include IMS contraindications (infection in the area, pregnancy, bleeding disorders, history of bacterial endocarditis, post-surgical implant in last four to six months and major surgery in the last three months), previous treatment with IMS or TCMA (for blinding purposes); true leg length difference of greater than ½” previous corticosteroid injections or recent fluoroquinolone use and systemic inflammatory disease. Those demonstrating the presence of other syndromes that cause pain in and around the Achilles tendon will be excluded by history-taking and physical examination: partial tearing, posterior ankle impingement/ os trigonum syndrome, tenosynovitis, dislocation of the peroneal or other plantar flexor tendons, irritation or neuroma of the sural nerve or insertional Achilles pain. Patients will be randomized by the research assistant ([name]) who is blinded to the patient’s baseline data using a random number generator (SPSS v.16.0).

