**[name]**

Oversee recruitment strategy, distribution of posters and study materials. Conduct initial phone screen (with [name] and [name]).

Conduct physical assessment screen.

Obtain informed consent. (Documents to be stored in locked cabinet at Kinetic for collection by HD).

Create tracking sheet for ankle range measures, VISA-A questionnaires (n= 4 x 42 = 168), Global Improvement scales (n= 4 x 42 = 168), and unblinding sheets for [name] and deliver to locked cabinet at Kinetic.

Collect ultrasound tissue characterization (UTC) images.

Interpret UTC images (with [name]).

Provide dry needling and exercise treatments and progressions.

Report unexpected events (per UBC Nov 11 2012 policy) to [name].

Track study expenditures.

Remain blinded to VISA-A / Global Improvement scores / ROM scores.

Record patient attendance dates and store in locked cabinet for [name] to access and record on Master Tracking Sheet.

Ensure data stored securely.

Deliver data from Canopy to Kinetic for collection by HD.

Primary contact in case of adverse event.

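### The therapist who gives the needling also acquires and jointly reads the UTC scans on a subjective criterion, with no masking stated, so the pilot remodelling signal is open to reader bias

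*Protocol*

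**What the plan says.** Outcome measures (Protocol) adds UTC to the clinical outcomes as a pilot: "After 12 weeks and 6 months of intervention, UTC scanning will be conducted". The stated aim is to see "whether there is any subjective indication of a potential effect of IMS on tissue remodeling" that a later mechanistic study might follow up. No scale, threshold or quantitative UTC measure is named.

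Study Team and Roles lists three tasks under one person: "Collect ultrasound tissue characterization (UTC) images", "Interpret UTC images (with" a named colleague, and "Provide dry needling and exercise treatments and progressions". A second investigator, whose other duties include ethics, data audits and liaison with the statisticians, has the matching task of joint interpretation. Nothing is said about whether that reader knows the allocation.

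The treating therapist is to be kept from the VISA-A, global improvement and range-of-motion scores. Scientific rigor concedes that this therapist cannot be blinded to treatment.

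Study Design requires at entry "evidence of midportion Achilles tendinopathy on physical examination and tendinosis on ultrasound", without saying whether that ultrasound is a UTC scan.

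**The concern.** Three features come together: a subjective criterion, a reader who knows the arm because that reader gave the treatment, and no stated masking. A reader who expects needling to help can lean towards seeing remodelling in the needled tendons, without any intent to do so. With no fixed scale, nothing limits that tendency.

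What is at stake is narrow. The only use the Protocol gives the UTC reading is to suggest whether tissue remodelling deserves a mechanistic study. The arrangement as written can produce such a suggestion when no effect exists.

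There is a secondary question of timing. Remodelling is a change over time, and the text places UTC scans only at 12 weeks and 6 months. If no time-zero image is kept, change within a tendon cannot be rated.

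**Working it through.** The Protocol gives no UTC effect, variance or sample size, so it has no figure of its own to reproduce. The main check is a comparison of sections.

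**Who reads, and what they know**

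| Measure | Assessed by | Allocation known to assessor? | Source |
|---|---|---|---|
| Dorsiflexion range | Separate physiotherapist | No, blinding required | Outcome measures; Study Team and Roles |
| VISA-A, global improvement | Participant; treating therapist kept from scores | Treating therapist not involved in rating | Study Team and Roles |
| UTC images | Treating therapist and second investigator | Therapist: yes. Second reader: not stated | Study Team and Roles; Scientific rigor |

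The link between needling and scanning is explicit. Both tasks stand under one role, and the research assistant's task list attaches to the UTC scans the same initials that the IMS treatment group section gives for the needling. The Protocol guards the other outcomes against the therapist's knowledge and leaves UTC without that guard.

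**When scans are taken**

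- Clinical measures: "These measures will be taken at 0 and 12 weeks, as well as at 52 weeks".
- UTC: "After 12 weeks and 6 months of intervention, UTC scanning will be conducted to determine, as a pilot study".
- Entry: an ultrasound is required, with the modality unstated.

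Week 0 is named for the clinical measures and not for UTC.

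**Illustration of size (assumed rates)**

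Inputs from the Protocol's Statistical analysis section: 42 enrolled, so 42/3 = 14 per arm; 11 per arm (33 in total) needed for analysis.

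Assumptions, none from the Protocol: one scan per participant rated improved or not; a 30% improved rate in every arm with no true effect; a fraction *u* of the non-improved IMS scans upgraded by a biased reading; a gap of at least 4 scans over one control arm taken as an apparent signal; independent readings.

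Apparent IMS rate: p = 0.30 + 0.70 × u, which gives 0.30, 0.37, 0.44 and 0.51 for u = 0, 0.1, 0.2 and 0.3.

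Chance of a signal: P(X − Y ≥ 4), with X ~ Binomial(n, p) and Y ~ Binomial(n, 0.30).

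| u | n = 14, one control | n = 11, one control | n = 14, both controls |
|---|---|---|---|
| 0 | 0.073 | 0.050 | 0.025 |
| 0.1 | 0.155 | 0.107 | 0.068 |
| 0.2 | 0.273 | 0.191 | 0.147 |
| 0.3 | 0.418 | 0.302 | 0.265 |

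The last column requires the IMS count to exceed each of the two control counts by at least 4. It is smaller throughout but rises in the same way.

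**The case against.** The strongest reply is that little hangs on this. UTC is labelled a pilot. It is not among the listed secondary outcomes, and it does not appear in the Statistical analysis section. Scientific rigor ties a larger study with more attention to mechanisms to a clinically significant effect of IMS, not to the UTC reading. All of this stands, and it limits the seriousness of the point.

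Some stronger readings that a reader might infer are not supported:

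- *The therapist is the sole reader.* Two roles carry the interpretation task. A joint reading with an unmasked provider is still not a masked reading, but the second reader may dampen the bias, and the illustration makes no allowance for that.
- *No baseline UTC scan exists.* The visible text names none, but the entry ultrasound may be a UTC scan, scan appointments are referred to a Master Tracking Sheet that is not shown, and the study flow chart did not survive conversion. Absence is not established.
- *UTC cannot measure change.* This holds only if there is no time-zero image. Even then, randomised arms can be compared at follow-up; chance differences at entry cost precision but are not a systematic bias.
- *The efficacy result is compromised.* No clinical outcome depends on the UTC reading.

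It is also fair to say that the illustration shows only that an assumed bias produces a biased result. It gives a sense of scale and is not evidence that such a bias will occur.

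**Conclusion.** The point holds for the reading of the scans. As written, the plan has the unblindable treating therapist acquire the UTC images and share in interpreting them on an expressly subjective criterion, without stated masking of arm or time point. This is an assignment that the Protocol itself makes, not a detail left for later.

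The consequence is confined to the pilot remodelling signal. Its size is unknown. Under the assumed rates, the chance of a spurious signal against one control arm goes from 7% to between 16% and 42% with 14 per arm, and from 5% to between 11% and 30% with 11. The direction follows from the design; the numbers rest wholly on the assumptions.

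On timing, the supportable conclusion is that the text leaves unclear whether a UTC image at entry exists. That calls for clarification and is not an established flaw.

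**What to change.** In Study Team and Roles and in Outcome measures:

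1. Have the research assistant export all UTC scans under a random code, without arm or date, and hold the key until rating is complete.
2. Have the second interpreter already named, stated to be masked to allocation, rate the coded scans in random order on a scale fixed beforehand. Each image is scored on its own, and any change is worked out after decoding. The treating therapist takes no part in the rating.
3. State whether the entry ultrasound is a UTC scan kept as time zero. If it is not, limit UTC conclusions to comparison between arms at follow-up and make no claim about change within a tendon.

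No new reader, patient or procedure is needed. The cost is some file handling and the loss of the therapist's input to the reading. Because the therapist would still acquire the images, coding removes bias in the reading but not any bias in acquisition; a sentence acknowledging this would be enough for a pilot measure.
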